**Methods/Design:**

This study has a prospective, randomized, double-blind, controlled, parallel-group design. Eligible patients are randomly assigned to one of the two treatment study groups, labelled the ‘melatonin group’ or the ‘placebo group’. A dose of 3 mg of oral melatonin or placebo is administered at 9:00 pm on four consecutive days. Earplugs and eye masks are made available to every participant. We plan to enrol 198 patients. The primary outcome is the objective sleep quality measured by the 24-hour polysomnography. The secondary outcomes are the subjective sleep quality assessed by the Richards Campbell Sleep Questionnaire, the anxiety level evaluated by the Visual Analogue Scale-Anxiety, the number of delirium-free days in 8 and 28 days, the number of ventilation-free days in 28 days, the number of antibiotic-free days, ICU length of stay, the overall ICU mortality in 28 days and the incidence and severity of the side effects of melatonin in ICU patients. Additionally, the body stress levels, oxidative stress levels and inflammation levels are obtained via measuring the plasma melatonin, cortisone, norepinephrine, malonaldehyde(MDA), superoxide dismutase(SOD), interleukin-6 (IL-6) and interleukin-8 (IL-8)concentrations.

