## Background

Sleep deprivation is a major concern in critically ill patients in intensive care units (ICU). Several studies have shown that poor sleep quality and the inability to sleep are the second largest stressors and rank among the top three major sources of anxiety during ICU stays
[1–3]. Sleep for ICU patients is characterised by frequent disruptions, loss of circadian rhythms and a paucity of time spent in restorative sleep stages. Typical findings described by polysomnography (PSG), the gold standard of assessing sleep quality, include increased latency, a higher proportion of non-rapid eye movement (NREM) sleep stage 1 and 2 (or light sleep), and reduced restorative slow wave (SW) and rapid eye movement (REM) sleep, largely because of frequent waking. Although ICU patients may experience normal or near normal total sleep time (TST), approximately 50% of this sleep occurs during the daytime
[4, 5]. In a recent observational study by Elliot *et al.* a 24-hour PSG was used to evaluate the sleep quality in ICU patients
[5]. They found that despite improvements in ICU design, technology and healthcare personnel training, there has been no improvement in the ICU sleep problem
[5–7]. It has been found that there are many extrinsic and intrinsic factors of sleep deprivation in the ICU setting including noise, light, nursing procedures, the presence of existing diseases, inflammatory mediators, anxiety, pain, sedative and opioid medications and mechanical ventilator setting
[8–12]. Furthermore, the occurrence of ICU sleep deprivation is associated with detrimental outcomes, including delirium, difficulty weaning, increased nosocomial infections, prolonged ICU length of stay (LOS) and increased ICU mortality
[13].

Conversely, despite the poor sleep quality that disturbs almost all ICU patients, clinicians remain reluctant to administer traditional sedative-hypnotic drugs in patients with sleep disorders. The major concerns are the side effects of these drugs, mainly that they destroy the structure of sleep, reduce the clinician’s ability to monitor the level of consciousness, induce respiratory depression and lower blood pressure
[14].

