**Table 1 Tab1:** **Definition of study objectives**

Objective	Definition
Objective sleep quality	Total sleep time, the length of sleep at night (9:00 pm - 7:00 am) and during the day (7:00 am - 9:00 pm), sleep architecture (NREM stage 1 and 2, SWS, REM), and sleep disruption (the number of arousals and duration of sleep), which will be monitored for one 24-hour period using a portable PSG device.
Subjective sleep quality	The subjective feelings of nightly sleep status of the patient, including sleep depth, wake time after sleep onset, number of awakenings after sleep onset, latency to sleep onset, and sleep quality. It will be evaluated using the RCSQ [38, 39].
Anxiety level	ICU anxiety is defined as a state marked by apprehension, agitation, increased motor activity, number of arousals, and fearful withdrawal during the ICU stay [40]. It will be assessed using the VAS-A.
Delirium-free days in 8 and 28 days	Number of days that the patient is not delirious over 8 and 28 days starting from the day of inclusion. Patients are diagnosed as delirious when they have at least one positive CAM-ICU screening during their ICU stay. A delirium-free day is defined as a negative CAM-ICU screening during that day. In case a delirious patient is discharged from the ICU, a delirium-free day is defined as a delirium observation scale score of less than 3 during a complete day [41].
Ventilator-free days in 28 days	Time in days that the patient is not on a mechanical ventilator. If the patient is ventilated mechanically, including invasive and non-invasive ventilation several times during one ICU admission, then the non-ventilator times are added. Ventilator-free days (in 28 days) will be calculated.
Antibiotic-free days in 8 and 28 days	Number of days that the patient does not require any antibiotics at 8 and 28 days from randomization will be calculated.
ICU length of stay	Duration of admission to the ICU.
Overall ICU mortality at 28 days	Survival time will be assessed. Patients will be classified as either alive at study day 28 or dead at study day 28. Differences between the two strategies in mortality rates will be evaluated using the assumption of asymptotic normality. Estimates of relative risks and odds ratios and the corresponding 95% confidence intervals will be presented.

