Side effects	Headache, dizziness, nausea, and drowsiness, determined daily by physical examination by the intensivist, and withdrawal symptoms upon discontinuation evaluated after the drugs are stopped.

NREM, None rapid eye movement; SWS, Slow wave sleep; REM, Rapid eye movement; PSG, Polysomnography; RCSQ, Richards Campbell sleep questionnaire; VAS-A, Visual analogue scale-anxiety; CAM-ICU, The confusion assessment method for the intensive care unit.

The primary outcome will be to determine the effect of melatonin administration on the 24-hour sleep-wake cycle and subjective sleep quality, including night/day sleep time, total sleep time(TST), percentages of NREM stage 1/2, slow wave sleep(SWS) and REM, the incidence of arousals per hour, the duration of sleep without waking and the number of sleep periods.

The secondary outcomes will be: (a) objective sleep quality as assessed by the Richards Campbell Sleep Questionnaire (RCSQ); (b) anxiety levels measured using the Visual Analogue Scale-Anxiety (VAS-A); (c) stress levels via measuring the plasma melatonin, cortisone and norepinephrine; (d) levels of oxidative stress; (e) levels of inflammation; (f) the number of delirium-free days in 8 and 28 days; (g) the number of ventilator-free days in 28 days; (h) the number of antibiotic-free days in 8 and 28 days; (i) ICU length of stay; (j) overall ICU mortality at 28 days; (k) the incidence and severity of melatonin side effects in ICU patients.

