### Data collection and management

Trained staff will record data and fill in the web-based collection forms. At the moment of patient inclusion, patient data on demographic characteristics and the history of past illnesses will be collected: age, sex, height and weight, Acute Physiology and Chronic Health Evaluation II(APACHE II) score, Sequential organ failure assessment(SOFA) score, Glasgow coma scale(GCS) score, diagnosis, and comorbidities. Clinical, physiological and analytical variables such as vital signs (temperature (T), blood pressure (BP), heart rate (HR), and respiratory rate (RR)), routine ICU laboratory tests (white blood count (WBC), serum creatinine (SCr), blood urea nitrogen (BUN), alanine aminotransferase (ALT), and aspartate aminotransferase (AST)) will be recorded at the moment of inclusion. The duration of time of ventilation, ventilation mode, the number of days in delirium, the ICU length of stay and the names, dose, duration of use and time of last use of sedatives, analgesics medications and vasopressor drugs will also be recorded prior to study inclusion.

Furthermore, sleep-related baseline data, including objective and subjective sleep quality and anxiety levels should be recorded. Subjective sleep quality, including the TST, the length of sleep at night (9:00 pm to 7:00 am) and in the day (7:00 to 9:00 pm), sleep architecture (NREM stage 1 and 2, SWS and REM), sleep disruption (the number of arousals and the duration of sleep), will be monitored for one 24-hour period using a portable PSG device from day 1 9:00 pm to day 2 9:00 pm. The PSG remains the gold standard for sleep quality assessment. Electroencephalographs (EEG; O1/M2, C4/M1), electromyographs (EMG), electrooculographs (EOG; right and left) and electrocardiographs (ECG; lead II) will be recorded. The patients’ skin will be prepared according to standard techniques. Gold cup EEG electrodes will be placed at O1/M2 and C4/M1 according to the International 10 to 20 System. Two EOG electrodes will be used for the right and left eye movements. The EMG electrodes will be located over the right and left masseter (facial) muscles. The electrode application will be performed by the specialist.

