The subjective sleep quality refers to the subjective feelings of the nightly sleep status of the patients. The baseline nightly sleep perceptive quality (day 1 9:00 pm to day 2 7:00 am) will be evaluated using the RCSQ at 9:00 am on day 2. The RCSQ contains five 100 mm visual analogue scales (VAS): sleep depth, latency, awakenings, time awake and quality of sleep (higher scores indicate better sleep). The RCSQ was pilot tested in a medical ICU and validated with overnight PSG in medical ICU patients. In our study, patients who are unable to write were assisted; the patients used their current communication strategy to indicate where the investigator should mark the VAS.

Anxiety is defined as a state marked by apprehension, agitation, increased motor activity, arousal, and fearful withdrawal. The baseline anxiety levels are assessed on day 2 at 9:00 am via self-report using the 100 mm VAS-A, which is presented to patients with a vertical orientation such as a thermometer. The bottom of the scale is the statement ‘not anxious at all’ and the top is “most anxious ever.” Patients indicate their current level of anxiety in response to ‘How are you feeling today?’. The VAS-A score is the number of millimetres from the bottom edge of the line (not anxious at all) to the patient’s mark. The VAS-A and the Spielberger State Anxiety Inventory are correlated (r = 0.4916 to r = 0.8219), demonstrating concurrent validity.

During the intervention period (days 2 to 5), outcome-related data, such as the objective and subjective sleep quality, and the anxiety level should be recorded. Analyses are limited to the fourth day (day 5 at 9:00 pm to day 6 at 9:00 am) because the potential chronophypnotic benefits of melatonin are not immediate and may take at least three days to be realised. Therefore, objective sleep quality should be monitored for one 24-hour period using the PSG from day 5 at 9:00 pm to day 6 at 9:00 pm, and the associated parameters and methods as described in the ‘Methods/Design’ section. Meanwhile, the subjective sleep quality and anxiety levels should be evaluated at 9:00 am on day 6 and the related methods have been previously described. In addition, daily information including the vital signs and lab parameters, the SOFA score, neurological monitoring (RASS, CAM-ICU, and GCS), as well as the mode, parameter and duration of mechanical ventilation should be recorded.

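### The stated 12-hour analysis window (to 9:00 am on day 6) contradicts the 24-hour PSG recording and the 24-hour primary outcome

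*Protocol article*

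**What the plan says.** All references are to the protocol article.

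- **Analysis window.** Data collection and management: "Analyses are limited to the fourth day (day 5 at 9:00 pm to day 6 at 9:00 am". The reason given is that melatonin's effect on sleep may need at least three days to appear.
- **On-treatment recording.** The next sentence, which opens with 'Therefore', has objective sleep quality monitored for "one 24-hour period using the PSG from day 5 at 9:00 pm to day 6 at 9:00 pm".
- **Questionnaires.** The same paragraph places the RCSQ and the VAS-A at 9:00 am on day 6.
- **Baseline recording.** Same section: "using a portable PSG device from day 1 9:00 pm to day 2 9:00 pm".
- **Outcome definition.** Table 1 defines objective sleep quality by total sleep time, "the length of sleep at night (9:00 pm - 7:00 am) and during the day (7:00 am - 9:00 pm"), sleep architecture and sleep disruption, over one 24-hour period.
- **Primary outcome.** Abstract: "The primary outcome is the objective sleep quality measured by the 24-hour polysomnography". Study design and outcomes: "the effect of melatonin administration on the 24-hour sleep-wake cycle", with night and day sleep time and total sleep time among the listed components.
- **Evaluation period.** Trial interventions ends the period of sleep evaluation and treatment at 9:00 pm on day 6.

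**The concern.** The article's only explicit analysis window ends 12 hours before the recording does. It matches neither period on which the outcomes are defined: it is two hours longer than the night and half the length of the 24-hour period. Nothing in the article confines the window to particular outcomes.

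Three things are at stake:

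- Two named components of the primary outcome, daytime sleep and 24-hour total sleep time, have no valid on-treatment value if the rule is followed as written.
- The baseline recording covers 24 hours. Any baseline-to-day-6 comparison of a whole-period variable, such as the repeated-measures ANOVA of sleep variables in Statistical analysis might make, would set unlike windows against each other.
- With two candidate windows for one outcome, the choice could be made after the data are seen. Statistical analysis promises that the main analysis will be fully specified before unmasking.

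All-day sleep is also the trial's stated contribution. The Background and the Discussion both fault earlier studies for not monitoring it.

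**Working it through.** This is clock arithmetic on times stated in the article.

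**Inputs**

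| Item | Times | Source |
|---|---|---|
| On-treatment PSG | day 5 21:00 to day 6 21:00 | Data collection and management |
| Baseline PSG | day 1 21:00 to day 2 21:00 | Data collection and management |
| Night | 21:00 to 07:00 | Table 1 |
| Day | 07:00 to 21:00 | Table 1 |
| Analysis window | day 5 21:00 to day 6 09:00 | Data collection and management |

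**Step 1: reproduce the stated 24 hours.** Night = 10 h and day = 14 h, and 10 + 14 = 24 h. The PSG period and the Table 1 periods agree, and the baseline recording is also 24 h.

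**Step 2: overlay the analysis window.** 21:00 to 09:00 = 12 h, made up of the full 10 h night plus 2 h of day (07:00 to 09:00).

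**Step 3: what is left out.**
- Daytime: 14 − 2 = 12 h, and 12/14 = 85.7%.
- Whole recording: 24 − 12 = 12 h, and 12/24 = 50%.

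**Step 4: effect on each sleep variable, if the rule is followed literally.**
- Night sleep time: all 10 of 10 h are available, so it is unaffected.
- Day sleep time: 2 of 14 h are available, so it cannot be estimated.
- 24-hour total sleep time: 12 of 24 h are available, so it cannot be estimated.
- Stage percentages, arousals per hour, uninterrupted sleep and number of sleep periods: they can be computed, but over 12 h against 24 h at baseline.

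**Step 5: with the window ending at 9:00 pm on day 6.** All 24 h are covered, no daytime hours are lost, and follow-up matches baseline.

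**Step 6: weigh the texts.** One parenthesis ends at 9:00 am. Against it stand the next sentence, the evaluation period in Trial interventions, Table 1, and the primary outcome as given in the abstract and in Study design and outcomes. The parenthesis is the outlier.

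**The case against.** The strongest reply is that 9:00 am is simply a slip. The reason given in that sentence explains which day is analysed, not which hours. A 24-hour recording cannot follow, by way of 'Therefore', from a decision to analyse 12 hours. The questionnaires fall at 9:00 am in the same paragraph, which is a plausible source of the wrong time. The 24-hour intention is clear everywhere else.

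Most of this stands, and it decides how the point should be put. A reader might infer that the investigators chose to throw away the daytime recording; the documents do not support that. But a probable slip does not remove the problem. This is a rule in the methods, it is the only analysis window stated, and 9:00 am has a meaning of its own as the questionnaire time, so a reader cannot be sure which text governs.

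Four further inferences are tempting and should not be drawn:

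- **Night sleep is contaminated by two daytime hours.** Table 1 ends the night at 7:00 am, and nothing suggests summing it to 9:00 am.
- **A day/night ratio is lost.** No ratio is a listed outcome; night and day sleep are two separate lengths.
- **The treatment comparison is biased.** The shorter window would apply to both arms alike. It would distort a before/after comparison of totals, and only if someone set 12 h against 24 h; it does not by itself create a difference between arms.
- **A definite share of sleep is omitted.** The Background says of ICU patients in general that "approximately 50% of this sleep occurs during the daytime". Turning that into a loss for this trial means applying it to this weaning population and assuming how sleep spreads over the day. With a 50% daytime share, the omitted part could be anything from 0 to 50% of total sleep, so hours are the only firm measure.

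**Conclusion.** Wrong as written. The analysis window conflicts with the recording window in the next sentence, with the end of the evaluation period and with the definition of the primary outcome. Followed literally, it leaves out 12 of 14 daytime hours (85.7%), half of the recording. On-treatment daytime sleep and 24-hour total sleep time could then be neither estimated nor compared with the 24-hour baseline.

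The conclusion needs no assumption beyond reading the stated clock times as they stand. Its reach is limited: night sleep, the variable behind the sample size, is measured in full under either end time, so neither that variable nor the sample size is touched. Whether 9:00 am is a slip or a carry-over from the RCSQ and VAS-A cannot be settled from the article. Either way, the sentences must be reconciled before unmasking.

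**What to change.** Replace the parenthesis with a rule along these lines: *PSG analyses use the recording from day 5 9:00 pm to day 6 9:00 pm. Night (9:00 pm to 7:00 am), day (7:00 am to 9:00 pm) and 24-hour variables are derived in the same windows as at baseline. The RCSQ and VAS-A are assessed at 9:00 am on day 6.*

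This should not change which variables are primary. The order of the endpoints is a separate question, and correcting the end time does not require it.

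The cost is one sentence. The 24-hour recording is already planned, so no extra data, visits or patients are needed. The correction should be dated before unmasking.

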### Current sample size justification

Primarily, we expect an increase in the time of the patient’s night sleep after melatonin administration in ICU patients with sleep deprivation. Based on retrospective data from our institution in the same population (mean TST from the nightly sleep was 3.5 hours with a SD of 1.8 hours). A 20% (0.7 hour) difference in the nightly sleep time between the two study arms is considered clinically relevant and likely to influence practice. Using the Power Analysis and Sample Size for Windows software (PASS2000, NCSS, Kaysville, Utah, United States), we will need to study 82 experimental subjects and 82 control subjects to be able to reject the null hypothesis that the population means of the experimental and control groups are equal with a probability (power) of 0.8 by the two-side paired *t*-test. The Type I error probability with testing this null hypothesis is 0.05. Assuming a dropout rate of 20%, 99 patients per group will be recruited.

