### Statistical analysis

All analyses will be performed according to the intention-to-treat principle, that is, all randomized patients will be analysed in the groups to which they were originally allocated and will be blinded to treatment assignment. Baseline patient characteristics will be compared and described using the appropriate statistics. Categorical variables will be presented as the numbers and percentages and will be analyzed by the *χ*^2^- tests or Fisher’s exact tests, or when appropriate, as relative risks. Continuous variables will be checked for normal distribution by the Kolmogorov-Smirnov test. Normally distributed variables will be expressed by their mean and standard deviation; non-normally distributed variables will be expressed by their medians and 95% confidence levels. Comparisons of continuous variables will be performed using Student’s *t*-test for normally distributed variables and the Mann-Whitney U test for non-normally distributed variables. Appropriate (linear, logistic, or Poisson) regression will be generated for the identification of the determinants of outcomes and for the correction of baseline covariates.

One-way repeated measures analysis of variance (ANOVA) were used to determine differences in the sleep variables, the subjective sleep quality, anxiety levels and plasma levels of melatonin, cortisol and norepinephrine. Twenty-eight day mortality will be analysed according to the Kaplan-Meier method and the results will be compared with the log-rank test hazard ratios and reported with 95% confidence limits. The number of delirium-free days, ventilation-free days and antibiotics-free days will be tested by Student’s *t*-test for normally distributed data and the Mann-Whitney U-test for non-normally distributed data. The differences in adverse events between the intervention and placebo groups are used for safety analyses. All tests of significance will be at the 5% significance level and two-sided. All of the data in this trial will be assessed with SPSS Statistics version 20.0 (SPSS, Chicago, Illinois, United States). The main analysis will be fully specified before unmasking.

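### The 82 patients per arm give about 70% two-sided power, not the stated 80%; the named paired test does not fit two independent arms, and the dropout allowance leaves 79 per arm

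*Protocol article*

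**What the plan says.** All the inputs stand in the protocol article under Current sample size justification.

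- Retrospective data from the same unit: "mean TST from the nightly sleep was 3.5 hours with a SD of 1.8 hours".
- Target effect: "A 20% (0.7 hour) difference in the nightly sleep time between the two study arms is considered clinically relevant".
- Error rate: "The Type I error probability with testing this null hypothesis is 0.05".
- Power and test: "with a probability (power) of 0.8 by the two-side paired" t-test.
- Result: "we will need to study 82 experimental subjects and 82 control subjects to be able to reject the null hypothesis". The null hypothesis is equality of the two groups' population means.
- Inflation: "Assuming a dropout rate of 20%, 99 patients per group will be recruited", which gives the 198 in the abstract.

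The Statistical analysis section confirms the sidedness: "All tests of significance will be at the 5% significance level and two-sided". It compares continuous variables by Student's t-test or the Mann-Whitney test and also mentions regression to correct for baseline covariates. The design and randomization sections describe two parallel arms, allocated 1:1, with no matching and no crossover.

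**The concern.** The paragraph gives everything needed to recompute the sample size, and the result does not follow from it. Three things looked wrong. The number per arm is too small for a two-sided test. A paired test is named for a comparison between separate groups of patients. The recruited number falls below the evaluable target once the assumed dropout occurs.

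The Discussion describes the trial as powered to test its hypothesis and says a neutral result would be informative. A reader would judge such a result against a 20% risk of missing a 0.7 h benefit. If the real risk is above 30%, a neutral result says considerably less about melatonin than the protocol implies.

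**Working it through.** **Inputs** (all from Current sample size justification): difference 0.7 h, SD 1.8 h, two-sided alpha 0.05, power 0.80, two equal arms. Standardised difference d = 0.7/1.8 = 0.389.

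**1. Trying to reproduce 82**

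For two independent arms, the normal approximation is n per arm = 2(z_alpha + z_power)²/d².

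| Calculation | Result |
|---|---|
| Two-sided 5%, 80% power: 2(1.960 + 0.842)²/0.389² | 103.8, so 104 per arm |
| Same, by noncentral t | 104.8, so 105 per arm |
| One-sided 5%, 80% power: 2(1.645 + 0.842)²/0.389² | 81.8, so 82 per arm |
| Same, by noncentral t | 82.4, so 83 per arm |
| Two-sided 5%, 70% power, normal approximation | 82 per arm |
| Two-sided paired t-test, 1.8 h taken as the SD of the differences | 53.9, so 54 pairs |
| Two-sided paired t-test, 1.8 h as the SD of each measurement, correlation 0 | 106 pairs |
| Same, correlation 0.2 | 85 pairs |
| Same, correlation 0.25 | 80 pairs |

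The stated inputs do not return 82. The one-sided normal approximation does. A paired calculation comes to about 82 only with a within-pair correlation near 0.23, and the protocol gives none.

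**2. Power actually obtained for 0.7 h** (two-sided 5%, independent arms, noncentral t)

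| Evaluable per arm | Power |
|---|---|
| 79 | 68.1% |
| 82 | 69.7% |
| 99 (no loss at all) | 77.7% |
| 105 | 80.1% |

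**3. The named test**

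A paired t-test needs two linked measurements per unit, and its variance is that of the within-pair difference. The stated null hypothesis concerns the means of two separate groups, and the trial does not match patients. A paired test could address before-after change within one arm, but that is not the treatment comparison. The protocol gives no SD of change.

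**4. Dropout**

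- Plan's figure: 82 × 1.2 = 98.4, rounded up to 99.
- Left after 20% loss: 99 × 0.8 = 79.2, about 79 and below the target of 82.
- Correct inflation of 82: 82/(1 − 0.2) = 102.5, so 103.
- Correct inflation of 105: 105/0.8 = 131.25, so 132 per arm, 264 in total.

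**5. What 198 randomised can detect**

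With 79 per arm, 80% two-sided power corresponds to a difference of 0.81 h by noncentral t (0.80 h by the normal approximation). 0.81/3.5 = 23% of the reference mean, against the 20% planned.

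**6. Effect of baseline adjustment**

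An analysis of covariance on the baseline sleep recording reduces the residual SD to 1.8 × √(1 − r²), where r is the correlation between baseline and follow-up. The protocol gives no r, so the range below is an assumption. Power at 79 per arm is:

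- r = 0.2: about 70%
- r = 0.4: about 76%
- r = 0.5: about 80%

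At 82 per arm, 80% needs r of about 0.47.

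**The case against.** The strongest reply is that the planned analysis may be more efficient than an unadjusted t-test. A baseline 24-hour sleep recording is scheduled for every patient, and the analysis section provides regression for baseline covariates. With a baseline to follow-up correlation of about 0.5, 79 per arm would have 80% power after all. This is fair as far as it goes, and it means the 30 to 32% type II error belongs to the unadjusted comparison. It does not rescue the paragraph, because the sample size is not derived from an adjusted analysis and no correlation is stated.

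A second reply is that the one-sided origin of 82 is an inference. That stands. A paired calculation with an undisclosed correlation near 0.23 also gives about 82, and the one-sided match is exact only by the normal approximation. Likewise, the 54 pairs assume that 1.8 h is the SD of the differences, whereas the protocol gives it as the SD of nightly sleep time. None of these routes is a valid two-sided comparison of independent arms with 80% power.

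Third, the dropout slip is small. It costs 4 patients per arm (103 against 99) and about 1.6 points of power (69.7% to 68.1%), and 82 would still be reached if dropout were no more than 17% (1 − 82/99 = 0.172). Agreed: alone it would be a minor correction.

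Fourth, intention to treat might be said to keep all 99. Even then unadjusted power is 77.7%. The protocol also expects losses: the consent section excludes withdrawn patients' data from analysis, and patients leave the study on ICU discharge, death or deterioration, possibly before the outcome recording on days 5 to 6.

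**Conclusion.** The concern holds. On the protocol's own inputs, an unadjusted two-sided comparison of independent arms needs 105 evaluable patients per arm, 23 more than the 82 stated. Power for 0.7 h is 69.7% at 82 per arm and 68.1% at the 79 left after the assumed 20% dropout, against the 80% claimed. The paired test contradicts both the stated null hypothesis and the parallel-group design. The dropout formula is wrong but adds little to the shortfall.

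These figures rest on the stated SD of 1.8 h, equal arms, a t-test and no baseline adjustment. Adjustment would bring power at 79 per arm to 80% only if the baseline to follow-up correlation is about 0.5 or more, which the protocol neither states nor supports. How the original figure arose cannot be settled from the document, and the conclusion does not depend on it.

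**What to change.** Rewrite the sample size paragraph so that test, sidedness, number and power agree:

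1. Delete the word paired and name a comparison of two independent arms.
2. State that 0.7 h, SD 1.8 h, two-sided 5% and 80% power require 105 evaluable patients per arm.
3. Compute dropout as n/(1 − d).
4. State what the actual size delivers: with 198 randomised and 20% loss (79 per arm), unadjusted two-sided power is 68% for 0.7 h, and 80% power applies to 0.81 h.
5. If analysis of covariance on the baseline recording is to be the primary analysis, say so before unmasking and state that 80% at 79 per arm requires a correlation of about 0.5 or more, with whatever supports that value. This is an option; items 1 to 4 are needed in any case.

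The cost is wording, and a less favourable power statement. The trial is already under way and the restatement needs no additional patients. Restoring 80% unadjusted power by recruitment would instead take 132 per arm, 264 in total, which is 66 more than planned.
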